**Figure 2 F2:**
[figure not shown]
Silicon nitride, titanium, PEEK and trabecular metal imaging characteristics in a human cadaveric vertebra (unpublished data).

The Valeo C+CSC cage has received the CE Mark based on preclinical testing and standards compliance, but has not been evaluated in a clinical study. Good clinical practice means that every new device should be compared to the golden standard prior to implementation of the device on a large scale. Therefore, it is necessary to perform a randomized controlled effectiveness trail on Valeo C+CSC versus PEEK cages. In the CASCADE (CAncelous Structured Ceramic Arthrodesis DEvice) trial, we will randomly and blindly compare anterior discectomy with ceramic cages versus anterior discectomy with PEEK cages. In this equivalence trial, we hypothesize similar effectiveness and no difference in clinical improvement between the ceramic cage and the PEEK cage as measured with the Neck Disability Index (NDI). Moreover, radiological properties will be documented focusing on fusion and subsidence.

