### Sample size and data analysis

Sample size for this equivalence trial has been established using power analysis incorporating data from journal article reports of similar ACDF studies. For sample size calculations, we have used the change in NDI from pre-op to one year post-op cited in the literature for ACDF with carbon fiber reinforced PEEK cages: 10% reduction (improvement) with a standard deviation of 22% [30]. The Minimal Clinically Important Difference (MCID) for the NDI is 7.5 points or 15% [31], which is the equivalence interval for sample size calculation. A 46-patient Valeo C enrollment has a power of .90 when compared with a PEEK study arm of the same size. Incorporating a one-year estimate of 8% loss to follow up, a total of 100 patients need to be enrolled.

The statistical significance of categorical data such as fusion will be tested using the Pearson Exact test. Parametric data will be evaluated using the Student’s t-test. The first data analysis will be performed when all of the 1-year follow-up data is available for the primary endpoint. The two groups will be considered equivalent if the mean NDI improvement for the silicon nitride cage group is within a range from the mean of the PEEK group minus the NDI MCID to the PEEK mean plus the MCID. A repeated measurements analysis of variance for the primary outcome measure will also be performed in order to compare the evolving patterns over time.

The inclusion period started in December 2011 and 2-year follow-up measures will be completed by the end of 2014.

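### Equivalence is judged on observed means alone, so a cage truly one full MCID worse passes half the time, and the stated power of .90 belongs to a different rule

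*Protocol article*

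**What the plan says.** All the relevant text is in the protocol article; no separate analysis plan is at hand.

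- **Hypothesis (Background).** "we hypothesize similar effectiveness and no difference in clinical improvement between the ceramic cage and the PEEK cage", measured with the NDI.
- **Margin (Sample size and data analysis).** "The Minimal Clinically Important Difference (MCID) for the NDI is 7.5 points or 15% [31], which is the equivalence interval for sample size calculation".
- **Power (same section).** "A 46-patient Valeo C enrollment has a power of .90 when compared with a PEEK study arm of the same size". The inputs are an SD of 22% for the one-year NDI change and 8% loss to follow-up, giving 100 enrolled. No alpha is stated.
- **Decision rule (same section).** The criterion reads: "considered equivalent if the mean NDI improvement for the silicon nitride cage group is within a range from the mean of the PEEK group", with limits one MCID either side of that mean.
- **Tests (same section).** "Parametric data will be evaluated using the Student’s t-test". A repeated measures analysis of variance of the NDI is also planned, to compare the course over time. Neither method is linked to the equivalence margin.

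**The concern.** An equivalence claim has to rule out, with stated confidence, true differences as large as the margin. The rule as written asks only whether the observed difference is smaller than the margin. An observed difference just inside the margin is about as likely to come from a true difference just outside it as from one just inside, yet the rule calls it equivalence.

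The named tests do not fill the gap. Student's t-test in its usual form has no difference as its null hypothesis, so a non-significant result does not show equivalence. The repeated measures analysis is not an equivalence test either.

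The power statement and the decision sentence also appear to describe different procedures. If so, the reader cannot tell what error rates the trial has been designed to have.

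This rule produces the trial's main conclusion, about a device that the article says has not yet been evaluated in a clinical study.

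**Working it through.** **Inputs**, all from the sample size and data analysis section unless noted:

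- SD of NDI change: 22% (11 points on the 0 to 50 scale)
- Margin: 15% (7.5 points)
- Evaluable patients: 46 per arm
- Loss to follow-up: 8%
- True difference for the power calculation: 0 (Background)
- Alpha: not stated, so one-sided 2.5% and 5% per test, and two-sided 5%, are all tried

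**Step 1. Standard error.** SE = 22 × √(2/46) = 4.59 percentage points. Margin/SE = 15/4.587 = 3.27.

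**Step 2. Reproduce the stated figures.** Enrolment: 92/0.92 = 100, as stated. Power with 46 per arm:

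| Rule | Formula | Normal | With t, 90 df | n per arm for .90 (normal) |
|---|---|---|---|---|
| Two one-sided 5% tests (90% CI inside ±15) | 2Φ(3.27 − 1.645) − 1 | 0.896 | 0.890 | 46.6 |
| Two-sided 5% test to detect a 15% difference | Φ(3.27 − 1.96) | 0.905 | 0.899 | 45.2 |
| Two one-sided 2.5% tests (95% CI inside ±15) | 2Φ(3.27 − 1.96) − 1 | 0.810 | 0.798 | 55.9 |
| Rule as written (observed difference inside ±15) | 2Φ(3.27) − 1 | 0.999 | not needed | 11.6 |

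The stated .90 with 46 per arm reproduces under either of the first two rows. It does not reproduce under the written rule, which would need only about 12 per arm for 90% power.

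**Step 3. Chance of declaring equivalence.** For a true difference δ, the written rule passes with probability Φ((15 − δ)/SE) − Φ((−15 − δ)/SE). The interval columns use the t distribution with 90 df.

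| True difference | Rule as written | 90% CI rule | 95% CI rule |
|---|---|---|---|
| 0 | 99.9% | 89% | 80% |
| 10% | 86% | 29% | 19% |
| 15% (one full MCID) | 50% | 5% | 2.5% |
| 17.5% | 29% | 1.4% | 0.6% |
| 20% | 14% | 0.3% | 0.1% |

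The 50% at the margin follows from the form of the rule. It hardly depends on the SD or the number of patients, and with 50 per arm it is still 50%.

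**Step 4. What the observed difference would have to be.** At the planned SD and size the half-width is 7.6% for a 90% interval and 9.1% for a 95% interval. The observed difference must therefore be below 15 − 7.6 = 7.4% (3.7 points) or 15 − 9.1 = 5.9% (2.9 points). The written rule accepts anything up to 15% (7.5 points).

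**Step 5. Conflict with the t-test.** Any observed difference between 9.1% and 15% would be significant at two-sided 5% and also count as equivalent. For example, an observed deficit of 14% gives t = 14/4.587 = 3.05, p = 0.003, and a 90% interval of 6.4% to 21.6%. The written rule would still declare equivalence.

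**The case against.** The strongest reply is that the sentence only describes the equivalence region and leaves the inferential procedure to a full protocol or analysis plan. The article speaks of an equivalence trial and a power analysis, and 46 per arm nearly matches two one-sided 5% tests, so an interval-based rule may have been planned and lost in condensation. That is possible, but the sentence is worded as the condition on which the groups will be considered equivalent, and following it would give the wrong conclusion. Nor does the near-match settle the intent, because an ordinary difference test fits .90 equally well.

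Three further points are fair:

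- The article nowhere says that a non-significant t-test will be read as equivalence, and two one-sided tests are themselves t-tests. The t-test sentence is therefore not an error in itself; it simply does not supply the missing procedure.
- The sample size is not shown to be wrong. The power mismatch is the same omission seen from the other side.
- With no alpha stated, the choice of a 90% interval is a recommendation and cannot be read out of the document. The cost of the alternative should be shown.

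**Conclusion.** The concern holds. As written, the rule for the primary conclusion ignores sampling error. It has a 50% false-equivalence rate at a true difference of one MCID, compared with 5% or 2.5% under an interval rule. Its power at zero difference is 99.9%, so the stated .90 describes some other rule. The document cannot show which one.

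The size of the error at the margin does not rest on the planning assumptions. The other figures assume an SD of 22%, 46 evaluable patients per arm and approximately normal means. The planned 46 per arm and 100 in total remain adequate for a 90% interval rule, so the fault lies in the decision rule and its mismatch with the power statement. It must be corrected before the one-year analysis.

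**What to change.** Replace the decision sentence with, for example: *Equivalence will be concluded only if the two-sided 90% confidence interval for the difference (ceramic minus PEEK) in mean 12-month NDI improvement lies entirely within −7.5 to +7.5 NDI points, corresponding to two one-sided tests at 5% each.* Add that a non-significant t-test is not evidence of equivalence, and restate the power and alpha for the chosen rule.

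The confidence level is for the sponsor to choose, and should be fixed before the one-year data are seen:

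- **90% interval:** power 0.89 with 46 per arm and no extra patients.
- **95% interval:** power 0.80 with 46 per arm. This also needs no extra patients if 0.80 is accepted. Keeping .90 needs 56 evaluable per arm by the normal approximation, or 112/0.92 = 121.7, so 122 enrolled.

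Either way the text change is one or two sentences.

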### Outcome assessment

Baseline assessments include demographics, work status, smoking status, neck and arm pain, history of neck trauma, medical history, pain medication, body mass index, and neurological signs and symptoms. A general physical and neurological examination is performed before the patient is enrolled into the study and will be repeated at each subsequent visit.

We will assess the below described validated outcome parameters. Patients will not be informed about their previous scores. Follow-up examinations will take place by the surgeon at 3 months, 6 months, 12 months, and 24 months after randomization. The schedule of follow-up visits, radiographic studies and outcomes measures is included in Table 2. The following measures of outcomes will be used:

1) Neck Disability Index (primary outcome measure): The NDI is a patient-completed 10-item questionnaire on 3 different aspects; pain intensity, daily work related activities and non-work related activities. Each item is scored from 0 to 5 and the total score ranges from 0 (best score) to 50 (worst score). The NDI is a modification of the Oswestry Disability Index and has been shown to be reliable and valid for patients with cervical pathology [21,22] and has been validated in the Dutch language [23].

2) Short-Form 36 (SF-36): The SF-36 [24] is a generic health status questionnaire that can easily be filled out by the patient at home. The questionnaire consists of 36 items on physical and social status of the patient subdivided in 8 domains; 1) physical functioning, 2) physical restrictions, 3) emotional restrictions, 4) social functioning, 5) somatic pain, 6) general mental health, 7) vitality and 8) general health perception. The questions are scored on a scale of 0 (worst health) to 100 (ideal health). This questionnaire has been used frequently and is validated in surgical studies on spine pathology [25,26].The Dutch language version has also been validated [27].

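### The repeated-measures ANOVA of NDI, read in its usual sense, leaves out any patient with a missed visit; a likelihood-based mixed model would keep them

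*Protocol article*

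**What the plan says.** The section on sample size and data analysis sets the primary decision at one year, on mean NDI improvement: "The two groups will be considered equivalent if the mean NDI improvement for the silicon nitride cage group is within a range" of one MCID either side of the PEEK mean. It then adds a second analysis of the same outcome: "A repeated measurements analysis of variance for the primary outcome measure will also be performed in order to compare the evolving patterns over time".

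NDI is scheduled before surgery and at four later visits. The section on outcome assessment states: "Follow-up examinations will take place by the surgeon at 3 months, 6 months, 12 months, and 24 months after randomization". Table 2 shows the same times.

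The only allowance for missing patients is in the sample size: "Incorporating a one-year estimate of 8% loss to follow up, a total of 100 patients need to be enrolled". No rate is given for loss between 12 and 24 months or for single missed visits. The article does not say how the repeated-measures model would be fitted, whether it runs to 12 or 24 months, or what happens to patients with incomplete scores.

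**The concern.** The article names a method, so the question is whether that method suits the data. Classical repeated-measures ANOVA needs a full set of scores from each patient. Someone seen at 3, 6 and 12 months but not at 24 months contributes nothing, although three of the four post-operative scores are in hand.

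The method also assumes sphericity, meaning that the differences between every pair of visits have the same variance. With gaps of 3, 6 and 12 months between successive follow-up visits this is doubtful. It bears on the tests of time and of treatment-by-time, and the second of these is the comparison of patterns that the sentence announces.

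At stake is the description of how the two arms evolve. The abstract says that the groups are followed for a second year to judge whether outcomes are stable, and this is the only method named in the article that addresses change over time. It could rest on a smaller group, selected by attendance, when the data for a better analysis are already being collected.

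**Working it through.** **1. The plan's own figure.** Inputs, all from the section on sample size and data analysis:
- SD of NDI change 22%: "10% reduction (improvement) with a standard deviation of 22" (per cent).
- Margin 15%: "The Minimal Clinically Important Difference (MCID) for the NDI is 7.5 points or 15% [31], which is the equivalence interval for sample size calculation".
- 46 per arm for power 0.90: "A 46-patient Valeo C enrollment has a power of .90 when compared with a PEEK study arm of the same size".
- 8% loss at one year.

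Alpha is not stated. I assume two one-sided tests at 0.05 each and a true difference of 0.

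- SE = 22 × √(2/46) = 4.59.
- Power = 2Φ(15/4.59 − 1.645) − 1 = 0.896, or 0.890 with the t distribution.
- At one-sided 0.025 each, power would be 0.81 (normal). The ordinary two-sided formula for a difference of 15 at 0.05 gives n = 46 per arm with power 0.905.
- Enrolment: 2 × 46 = 92, and 92 / (1 − 0.08) = 100.

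The stated figure is thus reproduced to within about one percentage point of power. The 8% loss is fully used in going from 92 to 100, and it refers to one year.

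**2. Complete cases through 24 months.** The loss by 24 months and the rate of single missed visits are not in the article, so both are assumptions: 8% to 16% lost by 24 months, and 0% to 5% missed independently at each of the 3-, 6- and 12-month visits.

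Share complete = (1 − loss by 24 months) × (1 − miss rate)³

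| Lost by 24 months | Missed per earlier visit | Calculation | Complete of 100 |
|---|---|---|---|
| 8% | 0% | 0.92 × 1 | 92 |
| 16% | 0% | 0.84 × 1 | 84 |
| 8% | 5% | 0.92 × 0.95³ | 79 |
| 16% | 5% | 0.84 × 0.95³ | 72 |

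The exponent is 3 because loss by 24 months already removes the 24-month score. An exponent of 4 would count that visit twice.

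**3. A different assumption.** If misses are independent at all four visits, with no separate dropout term, the share is (1 − p)⁴. This gives 92, 81 and 72 of 100 for p = 2%, 5% and 8%, a similar range.

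**4. If the analysis stops at 12 months.** With the planned 8% lost and 0% to 5% missed at 3 and at 6 months, the range is 0.92 × 0.95² = 83 up to 92 of 100. At the upper end nothing is lost beyond what the plan allowed for.

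**The case against.** The strongest reply is that the article never says patients are excluded. The label is also used loosely for likelihood-based models that keep partly observed patients, and a journal article commonly leaves model fitting and missing-data rules to a fuller document. This stands in part: a reader might infer that the plan drops patients, and the text does not support that as fact. The point is conditional on the ordinary meaning of the words. It is still more than missing detail, because the article chose and named a method.

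A reader might also see a conflict with the expected 8% loss. There is none, because that loss was covered by enrolling 100 rather than 92.

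A reader might go further and infer that leaving out incomplete patients makes the arms look alike, which would be the harmful direction in an equivalence trial. The article does not support this either. Nothing in it shows that patients who do badly miss visits, and the arms would converge only if dropout differed between them in a particular way. This analysis has no equivalence margin, and the equivalence rule uses the one-year means.

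Two technical replies also stand. A complete-case comparison of arms is not always biased when data are not missing completely at random; it stays valid, for example, if missingness depends only on arm. Departures from sphericity can be handled by standard epsilon corrections, though these do not bring back excluded patients. Finally, a mixed model is itself biased if missingness depends on the unseen score.

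**Conclusion.** The point holds in a conditional and limited form. If classical repeated-measures ANOVA is meant, the comparison of NDI over time would use only patients with every analysed visit, about 72 to 92 of 100 through 24 months. Only the 8% in that range comes from the article; the 16% and the 0% to 5% are assumptions. The sample size gives no cover for losses after one year or for single missed visits.

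The analysis is supplementary, so the one-year equivalence conclusion is untouched. The direction of any bias cannot be stated. The case for change is that a better method for the same question uses data already scheduled. The change is worth making, but the trial's main result does not depend on it.

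**What to change.** Replace the sentence with a likelihood-based mixed model for repeated measures:
- **Outcome:** NDI at 3, 6, 12 and 24 months.
- **Terms:** treatment, visit, treatment-by-visit, baseline NDI and baseline-by-visit.
- **Covariance:** unstructured. With four visits this is 4 variances and 6 covariances.
- **Patients:** all those with at least one post-operative score.
- **Reporting:** the treatment difference with its confidence interval at each visit.

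The model is valid under missing at random and does not need sphericity. If the authors already intend such a model, the new wording only makes that plain.

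The cost is a sentence or two of analysis text and slightly more model specification. No new data, visits or patients are needed.

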## Discussion

A cervical radicular syndrome due to disc herniation is a well-known entity with an annual incidence rate of 83 per 100,000. Patients usually present with radicular arm pain and paraesthesiae, with or without neck pain. More than 90% of the patients have a favourable outcome with conservative treatment only [32] .Surgery is indicated whenever disabling pain persists. Anterior cervical discectomy (ACD) is the basic surgical treatment of patients with radicular pain caused by cervical disc herniation. In 1958, Cloward first described anterior cervical decompression with the use of autologous iliac crest interbody graft (ACDF) to maintain disc height [1]. Smith and Robinson developed a technique using iliac crest bone blocks that was the standard for many year [2].There is still controversy about the benefits of adding interbody fusion to the cervical discectomy technique [4,10,33,34]. Frequently surgeons perform ACDF to maintain disc height and cervical alignment, and promote bony fusion to prevent instability [25].

Various prospective randomised trials have been performed comparing anterior discectomy with additional interbody fusion [3-9]. These results suggest that interbody fusion may not be necessary in all cases. However, definite conclusions could not be drawn due to methodological flaws such as small sample size, non-homogenous patient population, undefined randomisation procedures and inconsistent outcome measures. Two large randomized trials are currently addressing the question of the value of adding fusion or cervical total disc replacements to the cervical discectomy procedure [35,36]. It is anticipated that ACDF will still be a viable choice for many patients even after these trials are completed.

Although there is no consensus on which interbody device to use, currently PEEK cages are considered as the golden standard for anterior cervical discectomy with fusion by many surgeons [15-19]. However, PEEK and titanium have some undesirable imaging characteristics that result in a demand for better cages with similar effectiveness. Figure 2 illustrates the superior imaging properties of MC^2^ ceramic material compared to PEEK, titanium and trabecular metal. Moreover, the CSC material fills the center hole for the purpose of providing a scaffold for bone ingrowth resulting in solid fusion and no subsidence of the cage. The CSC form of the material has performed well in an animal model [37] but the results and effectiveness need to be validated in humans. It is possible that solid fusion without signs of subsidence may lead to improved clinical outcome.

The present protocol of the CASCADE trial is designed to demonstrate the effectiveness and security of cancellous structured ceramic cages compared to the golden standard PEEK cages in patients treated with anterior cervical discectomy and fusion. Worldwide implementation of new devices should only be done after completion of randomized controlled trials. In our opinion, Level 1 evidence that government and health insurance organizations are demanding would not be possible without close cooperation between industry and researchers, but transparency is warranted and relevant conflicts of interest must be disclosed.

## Abbreviations

CASCADE: Cancellous structured ceramic arthrodesis device; ACDF: Anterior cervical discectomy with fusion; ACD: Anterior cervical discectomy; PEEK: Polyetheretherketone; CSC: Cancellous structured ceramic; MRI: Magnetic resonance imaging; CT: Computer tomography; NDI: Neck disability index; VAS: Visual analogue scale.
